## Abstract

****Background**:**

Frail older patients are at high risk of both thromboembolism and bleeding, making anticoagulant therapy challenging. Direct oral anticoagulants (DOACs) have largely replaced vitamin K antagonists because of comparable efficacy and lower bleeding risk. However, evidence supporting their use in frail older patients remains limited. Recent studies have demonstrated that a substantial proportion of frail older patients have DOAC plasma levels outside the expected on-therapy range, which may be associated with an increased risk of bleeding or thromboembolic events.

****Objectives**:**

The DOAC-FRAIL randomized controlled trial (RCT) aims to determine whether adjustment of DOAC therapy based on peak plasma concentrations improves the safety and efficacy of anticoagulant treatment compared with standard care in frail older patients.

****Methods**:**

The DOAC-FRAIL study is an international, multicenter, randomized controlled trial including frail older patients aged ≥70 years with a Clinical Frailty Scale score >3 receiving DOAC therapy. Participants are randomized to either a Single Cycle Measurement and Adjustment Strategy based on peak DOAC plasma concentrations or standard care. Patients with a life expectancy of less than 3 months or previous DOAC dose adjustment based on plasma level measurements are excluded. The primary outcome is the composite of bleeding events, including clinically relevant non-major bleeding, and thromboembolic events during 2 years of follow-up. Secondary outcomes include feasibility, determinants of deviant peak DOAC plasma concentrations, quality of life, cost-effectiveness, and all-cause mortality

****Results**:**

The DOAC-FRAIL trial is currently ongoing. Participant recruitment has been initiated, and study results are expected after completion of follow-up.

****Conclusion**:**

The DOAC-FRAIL RCT will provide evidence on whether a plasma concentration-guided DOAC dosing strategy improves clinical outcomes compared with standard care in frail older patients. The findings may contribute to more personalized anticoagulant therapy in this vulnerable population.

****Trial registration number**:**

EU CT-2025-521362-10-00.

## Introduction

1

When considering anticoagulant therapy in frail older patients, balancing efficacy and bleeding risk is a challenge as this population is at high risk of both thromboembolisms, including ischemic stroke, and bleeding. Nowadays, direct oral anticoagulants (DOACs) have largely replaced vitamin K antagonists (VKAs) for major indications like atrial fibrillation (AF) after clinical trials showing that DOACs are noninferior to VKAs [[1], [2], [3], [4]]. In addition, DOACs are also increasingly prescribed to frail older patients as their bleeding risk appears more favorable than with VKA therapy, with lower rates of intracranial and fatal bleeding. Moreover, DOAC therapy does not require routine laboratory monitoring or frequent dose adjustments, making its use more practical.

Nonetheless, only limited evidence is available for DOAC use in the frail older population because of their poor representation in major randomized controlled trials (RCTs). In fact, a Dutch RCT showed an increased risk of major bleeding without an efficacy benefit in frail older patients with AF switched from VKA to DOAC [5]. One explanation for this increased risk of bleeding is the altered pharmacokinetics of DOACs in this population. In a French observational study, a substantial proportion of older patients had DOAC-plasma levels outside the expected on-therapy range [6], an observation that was confirmed in our prior studies [7,8] and others [9,10]. For example, in our DOAC-FRAIL pilot study (*N* = 42) among frail older patients, a deviant DOAC peak plasma level, defined as “outside the expected on-therapy range,” was found in 54% of patients during acute hospitalization and in 31% at the outpatient clinic [8]. In addition, we found the same results in our DOAC-FRAIL nursing home study in which 40% of nursing home residents had a deviant DOAC peak plasma level (unpublished data). Continuing from these results, the recent study of Godino et al. [11] revealed marked associations between high DOAC-plasma levels and higher odds of bleeding and low DOAC-plasma levels and higher odds of thrombosis in a frail older cohort, which confirms previous study results [12,13]. With this in mind and considering the aging population and the subsequent increase in DOAC use among frail older patients, including nursing home residents, for whom guideline-based recommendations are lacking regarding the management of DOAC treatment, it is crucial to evaluate the efficacy and safety of DOAC use in this specific population. Therefore, more research is needed in the vulnerable older population to facilitate appropriate and safe DOAC use in this group.

When considering all elements, we hypothesized that adjustment of DOAC use based on DOAC peak plasma level determination would reduce (in particular) the bleeding risks seen in the FRAIL-AF [5] and the 4Levels Study [11] in the (frail) older population compared with standard of care DOAC administration. Therefore, we aim in the DOAC-FRAIL RCT to evaluate the efficacy of a single-cycle measurement and adjustment strategy based on DOAC peak plasma levels in the frail older population (including nursing home residents). Within this strategy, DOAC use will be adjusted (either dose adjustment or switch to another DOAC) when a deviant DOAC peak plasma level is measured, aiming to reduce the incidence of (in particular) bleeding (including major and clinically relevant nonmajor [CRNM] bleeding) and thromboembolism (more as safety endpoint).

The aim of this article is to promote methodological transparency, facilitate critical appraisal of the study design prior to availability of results, reduce the risk of selective reporting, and support harmonization and replication of future research in this field. In addition, given the limited evidence currently available regarding DOAC monitoring in frail older adults, we believe that sharing the design and rationale of this study is of relevance to the clinical and scientific community.

## Methods and Analysis

2

### Study design and objectives

2.1

The study is a 2-country, multicenter, prospective RCT. The primary objective is to evaluate the effect of a single-cycle measurement and dose adjustment strategy vs standard care. Specifically, we will investigate whether this strategy reduces the incidence of major and CRNM bleeding and thromboembolism in frail older patients (including nursing home residents). Secondary objectives are to investigate the feasibility of this single-cycle measurement and adjustment strategy, as well as the prevalence and determinants of deviant DOAC peak plasma levels in the frail older population, differences in quality of life, cost-effectiveness, and mortality between the intervention and control groups. Figure 1 shows the full timeline of the DOAC-FRAIL RCT in both arms.

**Figure 1 fig1:**
[figure not shown]
Timeline of the DOAC-FRAIL RCT, in which T0 represents the moment of inclusion, T1 the moment of bleeding or thromboembolism, and T2 the end of the study. DOAC, direct oral anticoagulant; FU, follow-up; RCT, randomized controlled trial.

### Setting and patient population

2.2

Patients attending the outpatient clinic of the internal medicine departments, in particular, the geriatric and vascular medicine outpatient departments, and the cardiology outpatient departments of different (academic and regional) hospitals in the Netherlands and Belgium, and residents of nursing homes affiliated to the Limburg Living Lab in Ageing and Long-Term Care, are potentially eligible if they meet the inclusion criteria. The inclusion criteria are: (1) aged ≥ 70 years, (2) chronic DOAC use (for AF/venous thromboembolism), (3) frailty (defined as a Clinical Frailty Score [CFS] >3), (4) able to visit the outpatient clinic (only applicable to community-dwelling patients) and (5) has the capacity to provide informed consent. Exclusion criteria are a life expectancy of < 3 months estimated by the attending physician or prior adjustment of DOAC use based on DOAC level measurement.

In addition, hospitalized patients admitted to the departments of internal medicine and cardiology in the same hospitals are potentially eligible. However, participants included during their in-hospital stay will be randomized after a sufficient time of medical stability, defined as minimally 5 to 7 days after discharge.

Within the DOAC-FRAIL RCT, there will be a representation of both DOAC-naïve (defined as patients who had previously received a total of ≤ 2 months of DOAC therapy) and DOAC-experienced patients.

### Sample size calculation

2.3

For the sample size calculation, we made the following assumptions. First, the risk reduction applies to the entire intervention group, as the intervention consists of a single-cycle measurement and adjustment strategy, irrespective of whether this leads to a dose adjustment or DOAC switch. Second, the yearly incidence of the composite endpoint is assumed to be 15% to 20% in the control group, based on the literature [14], and 10% to 15% in the intervention group, based on an estimated absolute reduction of 5% after the single-cycle measurement and adjustment strategy. With a 1:1 allocation and a 2-sided α level of 0.05, 686 to 905 participants are required in each treatment arm to have a power of at least 0.80. Considering a drop-out percentage of ∼10%, a total of 1509 to 1991 participants is required and will be included.

### Study procedures

2.4

#### Recruitment of participants and informed consent procedures

2.4.1

Participants will be recruited by their attending physician in the hospital, outpatient clinic, or nursing home. If an individual is deemed potentially eligible and expresses interest, they will be contacted by a member of the research team as soon as possible. During this contact, the participant will be verbally informed about the study, all questions regarding this study will be answered, and the participant will be provided with the relevant informational documents. After the participant has had sufficient time (a minimum of 7 days) to review the information, a follow-up call will be made to indicate whether the individual wishes to participate in the DOAC-FRAIL RCT. If the participant is willing to take part, the research team member will ask the participant to briefly summarize their understanding of the study to ensure they fully comprehend the nature of their involvement. After this confirmation, written informed consent will be obtained in the presence of a study team member. Informed consent will be obtained prior to any study related procedure being undertaken at screening. Informed consent will be written, dated, and signed by the person performing the interview and by the participant. The participant will be provided with a copy of the document by which informed consent has been given. Once the participant has been officially enrolled, a note will be added to their electronic patient record (EPR) to document their inclusion in the study.

#### Randomization and blinding

2.4.2

After written informed consent has been given, the coordinating investigator will randomly assign the participant using Castor electronic data capture software. For in-hospital participants, the randomization will occur after a medically stable situation. As we would like to ensure a balance in sample size across the intervention and control groups, we will use block randomization. Randomization will additionally be stratified by center and by new vs “experienced” users. Blocks will be randomly chosen to determine the assignment of all participants.

Blinding of study participants is not feasible, nor is blinding for health care providers. However, blinding will be implemented for outcome assessors.

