### Data analysis

2.5

After the first 100 patients in the intervention group have completed the single-cycle measurement and adjustment strategy, an analysis will be conducted to determine whether a second DOAC measurement is necessary, provided that the first DOAC measurement falls within the expected therapeutic range.

Baseline characteristics will be presented stratified by allocation. The primary analysis will be performed according to the intention-to-treat principle. In addition, a per-protocol analysis will be conducted. To evaluate whether the single-cycle measurement and adjustment strategy is superior to standard care with respect to the composite endpoint, a competing risks survival model according to Fine and Gray will be used to analyze time to first event, accounting for competing events. The effect of treatment will be expressed as hazard ratios with corresponding 95% CIs. The proportional subdistribution hazards assumption will be assessed using appropriate diagnostic methods. Recurrent events and their nature will be summarized descriptively. Depending on the distribution of event counts, additional analyses using Poisson regression may be performed to formally test differences in the number of events between groups.

Furthermore, the aforementioned analyses will also be conducted separately for new users and long-term users. In addition, subgroup analyses in participants aged > 70, > 80, and > 90 years will be performed. Last, participants requiring a switch to VKA will be excluded to perform subgroup analyses to evaluate the effect in participants who use a DOAC.

Two-sided *P* values < .05 will be regarded as statistically significant. Missing data will be imputed depending on the extent of missing data and the likely mechanism. Results will be expressed as odds/hazard ratios including 95% CIs.

Descriptive statistics will be used to present the prevalence of deviant DOAC levels. Logistic and linear regression analyses will be performed to estimate associations between potential predictors of deviant DOAC levels and actual levels (linear model) and a deviance indicator (logistic model). Mixed-effects regression models for repeated measures will be used to assess the effect of the intervention on quality of life over the course of follow-up. Fixed effects will be time, study group, their interaction, and a set of potential confounding variables.

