The feasibility and acceptability of the single-cycle measurement and adjustment strategy will be evaluated within a qualitative study. A cost–utility study will be performed to evaluate the cost-effectiveness of our intervention. Health care consumption will be collected from the EPRs and linked to Dutch unit costs. Kaplan–Meier survival curves will be used to visually represent the survival experience of participants in the 2 groups. To formally test differences in survival rates, Cox proportional hazards regression will be performed, adjusted for potential confounders (such as age, sex, and comorbidities).

Additional explorative analyses will be performed after stratification for eg, DOAC, new users vs experienced users, and adjustments due to DOAC peak plasma levels above and below the expected on-therapy range.

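### The primary Fine and Gray analysis, as described, leaves out the two factors used to stratify randomisation; accounting for them is a minor, nearly costless improvement

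*Protocol article*

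**What the plan says.** **Randomisation (protocol article, 2.4.2).** Allocation uses blocks, and "Randomization will additionally be stratified by center and by new vs" experienced users.

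**Primary analysis (2.5).** By intention to treat, "a competing risks survival model according to Fine and Gray will be used to analyze time to first event, accounting for competing events". The result is a ratio with an interval: "The effect of treatment will be expressed as hazard ratios with corresponding 95% CIs". No stratum or covariate is named.

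**Where user type is used (2.5).** The article adds that "the aforementioned analyses will also be conducted separately for new users and long-term users", and it lists user type again among the exploratory stratified analyses. It is not given as a term in the overall comparison. Centre is not mentioned anywhere in 2.5.

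**Where adjustment is named (2.5).** For quality of life: "Fixed effects will be time, study group, their interaction, and a set of potential confounding variables". For mortality: "Cox proportional hazards regression will be performed, adjusted for potential confounders (such as age, sex, and comorbidities". Neither description lists the randomisation factors.

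**The concern.** Stratified blocks make the arms more alike on centre and user type than simple randomisation would. If those factors predict the outcome, the treatment estimate varies less from trial to trial than an unadjusted model assumes, so its test rejects a little too rarely. Separately, in a hazard model, leaving out a prognostic factor moves the estimated hazard ratio towards 1.

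Prognostic strata are plausible here. Section 2.2 recruits from nursing homes, academic and regional hospitals, and several types of clinic in two countries. At stake are a modest amount of power and an avoidable later choice between an adjusted and an unadjusted primary estimate. Recruitment has already begun.

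**Working it through.** **1. The plan's own figure.** Section 2.3 gives: "With a 1:1 allocation and a 2-sided α level of 0.05, 686 to 905 participants are required in each treatment arm". The formula is n = [1.96·√(2·p̄·(1−p̄)) + 0.842·√(p₁(1−p₁) + p₂(1−p₂))]² / (p₁−p₂)².

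- 15% vs 10%: (1.96·√0.21875 + 0.842·√0.2175)² / 0.0025 gives 686.
- 20% vs 15%: (1.96·√0.28875 + 0.842·√0.2875)² / 0.0025 gives 905.4, so 906 rounded up (stated: 905).
- Totals: 2 × 686 × 1.10 = 1509 and 2 × 905 × 1.10 = 1991, as stated.

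The figure reproduces. It is a plain comparison of two proportions that takes no credit for adjustment, so this point does not affect it.

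**2. What accounting for the strata would change.** The check simulated 2000 trials per setting.

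- From the plan: 1372 patients (2 × 686), control rate 15% per year, 2 years of follow-up, two-sided 5% test, and blocks within centre by user type.
- Assumed, because the documents give no figures: 15 or 40 centres, 30% new users, blocks of 4, the spread (SD) of centre effects on the log hazard, the hazard ratio of new versus experienced users, and a true treatment hazard ratio of 0.75.
- Simplified: subdistribution hazards are proportional, and the only censoring is at 2 years.

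Each trial was analysed without strata and then stratified by centre by user type.

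| Centres | Centre SD | New-user HR | Type I error, unstratified → stratified | Power, unstratified → stratified | Change (points) |
|---|---|---|---|---|---|
| 15 | 0 | 1.0 | 5.2% → 5.1% | 75.1% → 74.9% | −0.2 |
| 40 | 0 | 1.0 | 5.3% → 5.4% | 74.6% → 74.4% | −0.2 |
| 15 | 0.2 | 1.3 | 4.5% → 4.8% | 75.7% → 76.4% | +0.7 |
| 40 | 0.3 | 1.3 | 5.2% → 5.5% | 74.0% → 74.7% | +0.7 |
| 15 | 0.4 | 1.5 | 4.4% → 4.6% | 72.7% → 73.7% | +1.0 |
| 15 | 0.6 | 2.0 | 3.5% → 5.1% | 68.4% → 73.0% | +4.6 |

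Monte Carlo error is √(0.75 × 0.25 / 2000) ≈ 1.0 point on a power figure and √(0.05 × 0.95 / 2000) ≈ 0.5 point on a type I error. It is less on the power differences, because both analyses use the same simulated trials. Among the type I errors, only 3.5% is clearly below 5%.

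**3. Where the gain comes from.** It does not come from a smaller reported standard error. At hazard ratio 0.75 and 15 centres, that standard error rises slightly with stratification: 0.1098 to 0.1100 with no prognostic effect, 0.1108 to 0.1111 in the SD 0.4 setting, and 0.1115 to 0.1119 in the extreme setting. Two other things happen:

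- The estimate is less attenuated. In the extreme setting the mean log hazard ratio moves from −0.267 to −0.285, that is from exp(−0.267) = 0.766 to exp(−0.285) = 0.752.
- The conservatism goes. In the extreme setting with no treatment effect, the unstratified standard error averages 0.1048 against a true spread of 0.1002, which is 4.6% too large (0.1048 / 0.1002 = 1.046).

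Stratifying by user type alone in the extreme setting gives 69.4% power, so 1.0 of the 4.6 points comes from user type and the rest needs centre.

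**4. The planned effect.** If the yearly rates in 2.3 hold for both years, 686 per arm gives 686 × (0.2775 + 0.19) = 321 events at a hazard ratio of ln 0.90 / ln 0.85 = 0.65. Power is then Φ(|ln 0.65|·√(321/4) − 1.96) ≈ 97%. The upper rates (905 per arm, 577 events, hazard ratio 0.73) also give about 97%. On those assumptions there is little power left to gain.

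**The case against.** The strongest objection is that this reads silence as a decision. The article is a condensed account, it does not call the model unadjusted, and a list of model terms may well stand in a full protocol or analysis plan that is not shown. That limits the point: a reader might infer that the plan fixes a treatment-only model, and the text does not go that far. It does not remove the point, because 2.5 goes into adjustment for two secondary outcomes and names none for the primary one.

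A second objection also stands. Nothing in the documents says that centre or user type is prognostic. The balance mentioned in 2.4.2 is one of sample size, given as the reason for blocking, so it should not be said that the sponsor judged these factors prognostic. User type is not ignored either, since the analyses are repeated in new and long-term users. Those separate analyses do not, however, bring the factor into the overall comparison.

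Third, the unadjusted test remains valid, and part of the shift in the hazard ratio simply reflects that marginal and conditional hazard ratios are different quantities. This is correct, and it is why the point is minor.

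**Conclusion.** The point holds as a minor one. The analysis as described does not follow the randomisation, and any resulting error is on the conservative side: type I error is not inflated and the sample size is unaffected.

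Two stronger readings are tempting and are not supported. One is that the primary model's standard errors are too large and would shrink with adjustment. The reported standard error does not shrink. The unadjusted one exceeds the true variability clearly only when the strata are strongly prognostic. The other is that the plan gives up free power as a certainty. The change is about 0 to 1 point under none-to-moderate effects, including a trivial loss if the factors do not matter, and up to about 5 points only under extreme ones.

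These sizes rest on assumed centre numbers, block size, share of new users, prognostic strengths and a treatment hazard ratio of 0.75, none of which the documents give.

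**What to change.** State that the primary Fine and Gray model accounts for the randomisation factors: new versus experienced use as a stratum or covariate, and centre as strata. Pool small centres by a rule fixed in advance, for example by country and setting. Use the same factors in the per-protocol analysis and the mortality Cox model. Age and Clinical Frailty Scale, both collected at baseline, may be pre-specified as covariates, but this is optional and the mismatch does not require it.

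The cost is a sentence or two and no new data. There are two downsides: the pooling rule must be settled before results are seen, and the reported hazard ratio becomes conditional on the strata, which the report should say. If a full protocol or analysis plan already specifies these terms, it is enough to confirm it.

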#### Baseline data collection

2.4.3

In all patients, during the baseline visit, the following patient demographics and characteristics will be collected: medical history (Charlson Comorbidity Index [15]), weight, length, medication use, age, sex, frailty using the CFS [16,17], cognition using the Six-Item Cognitive Impairment Test [18], calf circumference, 4-m walk test and hand grip strength to screen for sarcopenia/low muscle mass, history of falling, Activities of Daily Living using the KATZ-score [19], Lawton Instrumental Activities of Daily Living score [20], living situation, CHA_2_DS_2_-VA (Congestive heart failure, Hypertension, Age, Diabetes, Stroke, Vascular disease, Age) and HAS-BLED (Hypertension, Abnormal renal/liver function, Stroke, Bleeding, Labile INR, Elderly, Drugs/alcohol) scores, and assessment of quality of life using the EQ-5D-5L questionnaire [21] (Supplementary Table 1). In addition, routine laboratory tests (creatinine and estimated glomerular filtration rate, hemoglobin and platelet counts, alanine transaminase and gamma-glutamyltransferase) will be performed. Information on bleeding and thrombosis history and medication adherence using the Medication Adherence Rating Scale 5 [22] will be collected.

